#### **8.12.2. Non-Serious Adverse Event Reporting Requirements**

All adverse events will be reported on the adverse event page(s) of the CRF. It should be noted that the form for collection of serious adverse event information is not the same as the adverse event CRF. Where the same data are collected, the forms must be completed in a consistent manner. For example, the same adverse event term should be used on both forms. Adverse events should be reported using concise medical terminology on the CRFs as well as on the form for collection of serious adverse event information.

#### **8.12.3. Sponsor Reporting Requirements to Regulatory Authorities**

Adverse events reporting, including suspected serious unexpected adverse reactions, will be carried out in accordance with applicable local regulations.

### **9. DATA ANALYSIS/STATISTICAL METHODS**

Detailed methodology for summary and statistical analyses of the data collected in this trial will be documented in a Statistical Analysis Plan, which will be dated and maintained by the sponsor. This document may modify the plans outlined in the protocol; however, any major modifications of the primary endpoint definition and/or its analysis will also be reflected in a protocol amendment.

#### **9.1. Sample Size Determination**

A total sample size of up to 18 healthy subjects has been chosen based on the need to minimize first exposure to humans of a new chemical entity and the requirement to provide adequate safety and toleration information at each dose level. Subjects who withdraw prior

to the completion of the study may be replaced at the discretion of the Sponsor. No formal inferential statistics will be applied to the pharmacokinetic, pharmacodynamic or safety data. These will be summarized descriptively.

## **9.2. Efficacy Analysis**

Efficacy analysis is not applicable to this trial.

## **9.3. Pharmacokinetic Analysis**

### **9.3.1. Analysis Populations**

All enrolled subjects with pharmacokinetic parameter(s) of interest for at least one period of the study will be included in the statistical analysis. Analysis sets may contain different numbers of subjects for different pharmacokinetic parameters based on availability of data. Individual and mean plasma PNU-100480, PNU-101603 and PNU-101244 concentration-time data will be tabulated and plotted as a function of dose.

### **9.3.2. Derivation of Pharmacokinetic Parameters**

The pharmacokinetic parameters for PNU-100480, PNU-101603 and PNU-101244 will be determined for each dose of PNU-100480 using non-compartmental methods, as data permit: maximum observed plasma concentration ( $C_{max}$ ), the time to  $C_{max}$  ( $T_{max}$ ), the area under the concentration-time curve from time 0 to the time of the last quantifiable concentration ( $AUC_{last}$ ), the area under the concentration-time curve estimated from time 0 to 24 hours ( $AUC_{24}$ ) and infinity ( $AUC_{inf}$ ) and the terminal phase half-life ( $t_{1/2}$ ). Also, the apparent oral clearance ( $CL/F$ ) and the apparent volume of distribution ( $V_z/F$ ) will be calculated for PNU-100480. PK parameters will be derived from the concentration-time profiles as follows:

**Table 10. Pharmacokinetic Parameters**

| Parameter    | Definition                                                                                                                        | Method of Determination                                                                                                                                                                                                                                              |
|--------------|-----------------------------------------------------------------------------------------------------------------------------------|----------------------------------------------------------------------------------------------------------------------------------------------------------------------------------------------------------------------------------------------------------------------|
| $AUC_{last}$ | Area under the plasma concentration-time profile from time zero to the time of the last quantifiable concentration ( $C_{last}$ ) | Linear/Log trapezoidal method                                                                                                                                                                                                                                        |
| $AUC_{inf}$  | Area under the plasma concentration-time profile from time zero extrapolated to infinite time                                     | $AUC_{last} + (C_{last} \cdot k_{el})$ , where $C_{last}^*$ is the predicted plasma concentration at the last quantifiable time point estimated from the log-linear regression analysis.                                                                             |
| $AUC_{24}$   | Area under the plasma concentration-time profile from time zero extrapolated to 24 hours                                          | Linear/Log trapezoidal method                                                                                                                                                                                                                                        |
| $C_{max}$    | Maximum plasma concentration                                                                                                      | Observed directly from data                                                                                                                                                                                                                                          |
| $T_{max}$    | Time for $C_{max}$                                                                                                                | Observed directly from data as time of first occurrence                                                                                                                                                                                                              |
| $t_{1/2}$    | Terminal elimination half-life                                                                                                    | $\text{Loge}(2)/k_{el}$ , where $k_{el}$ is the terminal phase rate constant calculated by a linear regression of the log-linear concentration-time curve. Only those data points judged to describe the terminal log-linear decline will be used in the regression. |
| $CL/F$       | Apparent clearance                                                                                                                | Dose/ $AUC_{inf}$                                                                                                                                                                                                                                                    |
| $V_z/F$      | Apparent volume of distribution                                                                                                   | Dose/ ( $AUC_{inf} \cdot k_{el}$ )                                                                                                                                                                                                                                   |

Actual PK sampling times will be used in the derivation of PK parameters. The relationship between relevant ECG parameters (eg, QRS and QT interval) and PNU-100480, PNU-101603 and PNU-101244 plasma concentrations will be explored graphically. If appropriate structural pharmacodynamic models may also be utilized to characterize these relationships using PK/PD approach.

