**Table 5. Projected Exposures of PNU-100480 (Parent Only) after Administration of Single Dose to Humans**

| Dose (mg) | C max (µg/mL) a | AUC total (µg·h/mL) b |
|-----------|---------------------------------------|----------------------------------|
| 35        | 0.014                                 | 0.157                            |
| 100       | 0.04                                  | 0.449                            |
| 300       | 0.12                                  | 1.35                             |
| 600       | 0.24                                  | 2.69                             |
| 1000      | 0.40                                  | 4.49                             |
| 1500      | 0.60                                  | 6.74                             |

aCmax was calculated using the expression  $C_{max} = (F \cdot \text{Dose} / V) \cdot e^{-K \cdot T_{max}}$ ,  $T_{max} = \ln(K_a / K) / (K_a - K) = 2.75$  Hr

bCalculated using the relationship  $AUC = \text{Dose} \cdot F / CL$ .

CL = 222,600 mL/hr for a 70 kg human, F = 1, V = 1771 L for a 70 kg human, Ka was assumed as 0.8 hr

**Table 6. Projected Exposures and Safety Margin of Parent (PNU-100480) and Two Metabolites (PNU-101603 and PNU-101244) Relative to Rat 100 mg/kg Dose Exposures after Administration of Single Dose of Humans**

| Dose (mg) | Combined C max (µg/mL) a | Safety Margin Using Total C max b | Combined AUC Total (µg·h/mL) c | Safety Margin Using Total AUC d |
|-----------|------------------------------------------------|---------------------------------------------------------|-------------------------------------------|--------------------------------------------|
| 35        | 0.18                                           | 81.94                                                   | 2.06                                      | 59.23                                      |
| 100       | 0.52                                           | 28.68                                                   | 5.88                                      | 20.73                                      |
| 300       | 1.57                                           | 9.56                                                    | 17.65                                     | 6.91                                       |

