### 9.3.3. Statistical Methods

No formal inferential statistics will be applied to the pharmacokinetic data.

The plasma PK parameters  $AUC_{inf}$ ,  $AUC_{24}$ ,  $C_{max}$ ,  $AUC_{last}$ ,  $T_{max}$  and  $t_{1/2}$  for PNU-100480 and its metabolite will be summarized descriptively by analyte, cohort, fasted/fed condition, and dose. Also,  $CL/F$  and  $V_z/F$  for PNU-100480 will be summarized descriptively by dose and fasted/fed condition. Plasma concentrations will be listed and summarized descriptively by analyte, cohort, dose, fasted/fed condition, and nominal PK sampling time. Individual

subject and median profiles of the plasma concentration-time data will be plotted by dose using actual and nominal times respectively for each analyte. Median profiles will be presented on both linear-linear and log-linear scales.

Dose normalized (to a 1 mg)  $AUC_{inf}$ ,  $AUC_{last}$  and  $C_{max}$  for PNU-100480 and its metabolite will be plotted against dose (using a logarithmic scale) and will include individual subject values and the geometric means for each dose. These plots will be used to help understand the relationship between the plasma PK parameters and dose.

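### Table 10 multiplies Clast by kel in the AUCinf formula where it must divide, so AUCinf, CL/F, Vz/F and the dose-normalised AUCinf plot are biased if programmed as printed

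*Protocol*

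**What the plan says.** Section 9.3.2 of the protocol states that the PK parameters will be derived by non-compartmental methods as set out in Table 10. The rows that matter are these:

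- **AUCinf, definition:** "Area under the plasma concentration-time profile from time zero extrapolated to infinite time".
- **AUCinf, method:** "AUC_{last} + (C_{last} \cdot k_{el", where Clast* "is the predicted plasma concentration at the last quantifiable time point estimated from the log-linear regression analysis". The asterisk appears in the definition but not in the formula.
- **Half-life:** ln 2 divided by kel, where kel "is the terminal phase rate constant calculated by a linear regression of the log-linear concentration-time curve".
- **CL/F:** dose divided by AUCinf.
- **Vz/F:** "Dose/ ( $AUC_{inf} \cdot k_{el", that is, dose divided by the product of AUCinf and kel.

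CL/F and Vz/F are calculated for the parent drug only. Section 9.3.3 plots AUCinf, AUClast and Cmax, each "Dose normalized (to a 1 mg" dose, against dose, and says of them: "These plots will be used to help understand the relationship between the plasma PK parameters and dose". AUC is reported in concentration times time, as in the Table 5 column "AUC total (µg·h/mL". The copies of Table 10 in Appendix 3 (Amendment 1) print the same product, and no other place in the protocol gives a different formula.

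**The concern.** The term added to AUClast should be the area under the curve beyond the last quantifiable sample. For a log-linear decline that area is the concentration at that point divided by the rate constant. The table multiplies instead. The rows of the table therefore do not fit together: kel is a rate constant for half-life and Vz/F, but is used in the AUCinf row as if it were a time.

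A program that followed the cell would drop nearly all of the extrapolated area. The loss would carry into CL/F and Vz/F, which Amendment 1 added at the regulator's request, and into the dose-normalised AUCinf plot. The loss also depends on how late the last quantifiable sample falls. If low doses became unquantifiable sooner than high doses, dose-normalised AUCinf would be pushed down more at the low end and could suggest a departure from dose proportionality that is not there.

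**Working it through.** **Units.** Half-life = ln 2/kel, so kel is in 1/h. Clast* is in µg/mL.

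- Printed term: Clast × kel is in µg/mL per h, which cannot be added to an AUC in µg·h/mL.
- Tail area: the integral from tlast to infinity of Clast* · exp(−kel(t − tlast)) equals Clast*/kel, in µg·h/mL.

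**Inputs.** From the Table 5 footnotes: CL = 222.6 L/h, V = 1771 L, F = 1, ka = 0.8 per h. From Section 3.2: projected half-life 5.5 h. From Sections 6.2.2 to 6.2.5: PK samples up to 48 h, and to 72 h in Cohort 1 Periods 2 and 3 and in all Cohort 2 periods. The protocol gives no lower limit of quantification, so each last quantifiable time below is an assumption.

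**Reproducing the plan's own figures.** k = 222.6/1771 = 0.1257 per h, and ln 2/0.1257 = 5.51 h, which agrees with 5.5 h. At 600 mg, AUC = Dose · F/CL = 600/222.6 = 2.695 µg·h/mL, against 2.69 in Table 5. The other five doses in Table 5 also reproduce.

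**Ratio of the two terms.** (Clast × kel)/(Clast/kel) = kel². With kel = 0.1257, kel² = 0.0158, so the printed tail is 1.6% of the true one, or 1/0.0158 ≈ 63 times too small. The factor holds with time in hours.

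**Effect on AUCinf.** I took a one-compartment oral profile at 600 mg with kel = ln 2/5.5 = 0.1260 per h and ka = 0.8 per h. It was integrated exactly to tlast, and the tail was then added both ways. For tlast = 12 h:

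- AUClast = 1.9903 and Clast = 0.0888 µg/mL.
- Product: 1.9903 + 0.0888 × 0.1260 = 1.9903 + 0.0112 = 2.0015.
- Division: 1.9903 + 0.0888/0.1260 = 1.9903 + 0.7049 = 2.6952.
- Ratio 2.0015/2.6952 = 0.743, so AUCinf is 25.7% low.
- CL/F is 1/0.743 − 1 = 34.7% high. Vz/F is high by the same percentage, because kel itself is unaffected.

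| tlast (h) | AUClast | As printed (×) | With division (/) | AUCinf too low | CL/F and Vz/F too high |
|---|---|---|---|---|---|
| 12 | 1.9903 | 2.0015 | 2.6952 | 25.7% | 34.7% |
| 16 | 2.2695 | 2.2762 | 2.6954 | 15.6% | 18.4% |
| 24 | 2.5400 | 2.5425 | 2.6954 | 5.7% | 6.0% |
| 36 | 2.6612 | 2.6617 | 2.6954 | 1.3% | 1.3% |
| 48 | 2.6879 | 2.6880 | 2.6954 | 0.3% | 0.3% |

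Only division returns the protocol's own Dose · F/CL whatever the last time (within 0.01% at 12 h).

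**Longer half-life.** The protocol gives no metabolite half-life. For an assumed 20 h, the same calculation gives as-printed to true ratios of 0.802 at tlast 48 h (20% low) and 0.914 at 72 h (9% low).

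**The case against.** The strongest objection is that the protocol may not say this at all. The cell defines Clast with an asterisk, yet the formula has none, and a single multiplication dot stands where the asterisk, or an asterisk and a slash, would be expected. A source reading Clast*/kel that was garbled when the PDF was converted is plausible. The matching copies in Appendix 3 were read in the same way and could share the fault. Slashes do survive in the half-life, CL/F and Vz/F cells, but none of those follows an asterisk. What stands is that the PDF page must be looked at. The text at hand prints the product consistently, so the point is not overturned.

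The second objection is that harm is unlikely. The definition column states the intent, standard non-compartmental software divides by default, a units check would expose the error, and all PK analysis is descriptive. The SAP, not shown, may also give the formula correctly. This lowers the severity. It does not remove the point, because the protocol has fixed a formula rather than left one open.

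A reader might also infer more than the documents support:

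- **Dose escalation.** One might conclude that exposure would be understated against the 122 µg·h/mL limit. Section 3.3 does not say that AUCinf is the human quantity compared with it, and the limit is itself a rat AUC(0-tlast) in Table 1. At 1000 and 1500 mg, where Table 6 shows the smallest AUC margins (2.07 and 1.38), sampling runs to 72 h. The parent error there is negligible if the late samples are quantifiable.
- **All dose-proportionality plots.** Only the AUCinf plot is affected. The AUClast and Cmax plots stand beside it unaltered.
- **An established false dose trend.** That requires low doses to fall below quantification earlier, and no assay limit is given to show it.

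**Conclusion.** The formula as printed is wrong. That follows from Table 10 alone, subject to confirming the source page. The tail term is about 63-fold too small at the projected kel. If the cell is programmed literally, AUCinf is understated for every analyte, CL/F and Vz/F are overstated for the parent, and the dose-normalised AUCinf plot is biased. AUClast, AUC24, Cmax, Tmax and half-life are untouched.

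The practical size is uncertain. For the parent at the projected half-life it runs from about a quarter of AUCinf (last time 12 h) to 0.3% (48 h). It is larger with late sampling only if an analyte has a long half-life, such as the assumed 20 h. These figures rest on the projected one-compartment model, assumed last times and literal use of the formula. With descriptive analysis throughout and no stated link to the escalation limit, this is a minor to moderate correction, not one that threatens the study's conclusions.

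**What to change.** 1. Check the PDF page of Table 10 to see whether the formula carries an asterisk or a slash that was lost in reading.
2. If the product is really printed, change the AUCinf cell to AUClast + (Clast*/kel), with Clast* the regression-predicted concentration already defined there.
3. In either case, confirm that the PK program divides by kel and uses the predicted rather than the observed last concentration.

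The cost is one table cell and a short program check. No visit, sample or procedure changes.

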### 9.3.3. Statistical Methods

No formal inferential statistics will be applied to the pharmacokinetic data.

The plasma PK parameters  $AUC_{inf}$ ,  $AUC_{24}$ ,  $C_{max}$ ,  $AUC_{last}$ ,  $T_{max}$  and  $t_{1/2}$  for PNU-100480 and its metabolite will be summarized descriptively by analyte, cohort, fasted/fed condition, and dose. Also,  $CL/F$  and  $V_z/F$  for PNU-100480 will be summarized descriptively by dose and fasted/fed condition. Plasma concentrations will be listed and summarized descriptively by analyte, cohort, dose, fasted/fed condition, and nominal PK sampling time. Individual

subject and median profiles of the plasma concentration-time data will be plotted by dose using actual and nominal times respectively for each analyte. Median profiles will be presented on both linear-linear and log-linear scales.

Dose normalized (to a 1 mg)  $AUC_{inf}$ ,  $AUC_{last}$  and  $C_{max}$  for PNU-100480 and its metabolite will be plotted against dose (using a logarithmic scale) and will include individual subject values and the geometric means for each dose. These plots will be used to help understand the relationship between the plasma PK parameters and dose.

#### **9.4. Pharmacodynamic Analysis**

##### **9.4.1. Whole Blood Bactericidal Activity (WBA)**

The absolute values and changes from baseline for WBA will be summarized descriptively (N, mean, median, minimum, maximum, standard deviation) by dose and time-points. These summaries will be calculated for each dose level cohort.

The relationship between WBA and PNU-100480 (or its metabolite) concentration may be explored graphically or statistically.

#### **9.5. Safety Analysis**

The safety analysis population is defined as all enrolled subjects who receive at least 1 dose of study medication.

Adverse events, ECGs, blood pressure, pulse rate, continuous cardiac monitoring, and safety laboratory data will be reviewed and summarized on an ongoing basis during the study to evaluate the safety of subjects. Any clinical laboratory, ECG, BP, and PR abnormalities of potential clinical concern as defined in Appendix 1 will be described. Safety data will be presented in tabular and/or graphical format and summarized descriptively, where appropriate.

Medical history and physical exam information collected during the course of the study will not be captured for inclusion into the study database, unless otherwise noted. However, any untoward findings identified on physical exams conducted after the administration of the first dose of study medication will be captured as an adverse event, if those findings meet the definition of an adverse event. Data collected at screening that is used for inclusion/exclusion criteria, such as laboratory data, ECGs and vital signs will be considered source data, and will not be captured for inclusion into the study database, unless otherwise noted. Demographic data collected at screening will be included in the study database.

Routinely collected laboratory safety data that are not required by the protocol will be considered source data, and suppressed at the point of mapping data from PIMS into PIMS data extraction views. However, unexpected data collected with specific medical intent (ie, the workup of an adverse event, etc.) that is not required by the protocol, will not be suppressed at the point of extraction from PIMS.

090177e180ac49ac\1.0\Approved\07-May-2009 14:41

Key data from the telemetry or Holter summary reports, including PVC frequency, PAC frequency, supraventricular couplets, ventricular couplets, occurrence, duration and morphology of ventricular tachycardia, and occurrence and type of AV block, will be captured electronically and transferred to a central database. The primary purpose of this collection is to allow the construction of a database summarizing the frequency of events in drug treated subjects and, more importantly, establish the background event rate in placebo treated subjects. The background event rate will permit the proper perspective to be placed on observations arising from future clinical studies. Cross-consistency between the database and the AE forms will not be checked. The database will be housed in Oracle Clinical under protocol NRA9990006, "Cardiac Telemetry Dataset Analysis," for the initial year that this guidance is in effect.

### **9.5.1. Electrocardiogram (ECG) Analysis**

#### **9.5.1.1. Derivation of Electrocardiogram Parameters**

The QT, heart rate, QTcB, QTcF, PR, RR, and QRS will be recorded at each assessment time indicated in the Schedule of Activities. If QTcF is not supplied then it will be derived using Fridericia's (QTcF) heart rate correction formula. If QTcB is not supplied then it will be calculated using Bazett's heart rate correction formula.

The average of the triplicate readings collected at each assessment time will be calculated prior to analyzing each ECG parameter. The average of the triplicate ECG measurements collected at predose on Day 1 will serve as each subject's baseline values. The maximum absolute value (postdose) and the maximum increase from baseline for QT, heart rate, QTcF, PR and QRS will be determined for each subject.

